#### Secondary endpoints

2.7.2

Secondary outcomes included rates of improvement in liver failure, hepatocellular carcinoma, liver disease-related mortality, liver fibrosis, cirrhosis, quality of life scores, improvement in laboratory markers, and adverse events.

#### Safety assessments

2.7.3

The researchers closely observed the physical condition of the participants and checked them accordingly before enrolling in the group. The investigator will record all adverse events on the case report form (CRF) and report them to the person in charge. At the same time, any serious adverse events will be reported to the ethical committee of Beijing Ditan Hospital within 24 h, and the medical expert committee will determine whether the adverse events are related to FZHY. Participants have the right to withdraw from their consent to participate in the study at any time for any reason. The investigator will record the timing of the adverse event, its severity, the duration of the disease, and the appropriate actions taken in response to the adverse event.

### Quality control and data management

2.8

Researchers will adhere to the clinical research system of quality control and quality assurance by adhering to their responsibility for the clinical research program, following standard operating procedures, and adhering to the clinical research system of quality control and quality assurance. Participants assignment in the study must conform to the designated random assignment scheme, and the processing grouping code for each participant will be stored confidentially by the statistical unit and the researcher.

All investigators will receive professional training, and investigators will follow good guideline clinical practices to ensure safety, blinding, and data quality. Investigators should ensure that all information is accurately and legally recorded in medical records and CRFs, and that two independent investigators assigned will double-check all CRFs. A synchronous electronic data acquisition (EDC) system will ensure real-time data entry and secure storage. The quality of data in the EDC system will be monitored by dedicated data management experts.

Ensure accurate recording of all laboratory metrics for data accuracy and authenticity. To assess data accuracy and procedural compliance, medical statisticians must accurately enter research data into reports and maintain all data management. Ethics committees at all research centers will oversee processes related to data access and analysis.

### Withdrawal criteria

2.9

Participants will withdraw from the trial if: (1) the patient has experienced a serious adverse event. (2) Patients with severe changes or complications were associated with the disease during the trial. (3) Patients were unable to comply with the study plan, resulting in incomplete medical management records. (4) Patients who voluntarily requested to withdraw from the trial.

### Sample size calculation

2.10

Sample size was calculated using a two-sided Z-test for two independent proportions with α = 0.05 and power = 80% (β = 0.20). Based on retrospective data, the 48-week cumulative incidence of further decompensation was 53.7% in patients who received commercial Chinese polyherbal preparation (CCPP) (including Fuzheng Huayu, Anluo Huaxian, or Fufang Biejia) plus antiviral therapy, and 67.5% in patients who received antiviral therapy alone. Applying these proportions to the current prospective trial (Fuzheng Huayu combined with antiviral therapy versus placebo combined with antiviral therapy) with a 1:1 allocation ratio, the required sample size per group was calculated as 194 using the formula. Accounting for a 10% dropout rate, we enrolled 216 patients per group, for a total of 432 patients. The calculation was performed using PASS 2021.
$$n=\frac{\left[{\left(Z_{\left\{\frac{\alpha }{2}\right\}}+Z_{\beta }\right)}^{2}\times \left(p1\left(1-p1\right)+p2\left(1-p2\right)\right)\right]}{{\left(p1-p2\right)}^{2}}$$
where 
$Z_{\left\{\frac{\alpha }{2}\right\}}$
 = 1.96 (for α = 0.05), Z_β_ = 0.842 (for β = 0.20, power = 80%)

### Data analysis plan

2.11

We used competitive risk analysis to ensure an accurate assessment of the cumulative incidence of specific events, Kaplan-Meier method was used for the survival curves of the two groups, and log-rank method was used for the comparison of the cumulative survival rates of the two groups. Continuous variables will be summarized as mean ± standard deviation or median with interquartile range. Within-group changes from baseline may be assessed using paired t-tests or Wilcoxon signed-rank tests, as appropriate. Between-group comparisons of changes from baseline will be performed using independent-sample t-tests or Wilcoxon rank-sum tests. The notational information of each visit of the two groups will be described statistically using frequency (percentage). Changes in the two groups before and after treatment were analyzed using the chi-square test. All statistical tests will be two-sided, and p < 0.05 will be considered statistically significant for the differences tested. Statistical analyses will be calculated using SPSS and SAS analysis software.

Analysis populations: Defined the ITT population as all randomized participants, analyzed according to their original randomized assignment regardless of whether they received the assigned treatment or completed the study. Defined the per-protocol (PP) population as participants who completed the 48-week treatment period without major protocol violations. In the ITT analysis, if the data related to the efficacy are missing, the method of last observation carried forward (LOCF) will be used to fill in.

Shedding analysis: Comparison of total shedding rate and shedding rate due to adverse events between the two groups will be done using chi-square test.

Balance analysis of baseline values: ANOVA or chi-square test will be used to compare demographic data and other baseline value indicators, and to measure how balanced the two groups are.

Adherence analysis: Adherence will be calculated as (actual dose taken/prescribed dose) × 100% over the 48-week treatment period. Good adherence is defined as adherence between 80% and 100% (inclusive). Participants with adherence <80% will be classified as having poor adherence. Participants with adherence >100% will be documented as protocol deviations and reviewed for safety; these participants will not be classified as good adherence and will be excluded from the per-protocol population. The chi-square test will be used to compare the proportion of participants with good adherence between the two groups.

Effectiveness analysis: For the primary time-to-event efficacy endpoint, a Cox proportional hazards model will be used to estimate the treatment effect, with treatment group as the main factor and study center included as a stratification factor or covariate, depending on the number of participants and events in each center. The Kaplan-Meier method and log-rank test will be used for descriptive and unadjusted comparisons. For binary efficacy outcomes, logistic regression adjusted for study center and relevant baseline covariates will be used. If some centers enroll only a small number of participants or have few outcome events, centers may be pooled according to prespecified rules before model adjustment.

Safety analysis: the chi-square test was used to compare the incidence of adverse events between the two groups and a list describing the adverse events that occurred in this study; the changes in normal/abnormal laboratory test results before and after the study as well as the relationship with the study drug in the event of abnormal changes.

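### The per-protocol set requires 48 completed weeks of treatment with no exception for death or withdrawal for complications, so membership depends on the outcome; the adherence rules share part of the problem

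*Protocol article*

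**What the plan says.** Section 2.11 (Data analysis plan) of the protocol article defines two analysis sets. ITT is everyone randomized, whether or not they were treated or finished. PP is "participants who completed the 48-week treatment period without major protocol violations". No exception is given for a patient whose treatment ends because of death or a clinical event.

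Section 2.9 (Withdrawal criteria) lists among the reasons for leaving the trial that "the patient has experienced a serious adverse event", and also "Patients with severe changes or complications were associated with the disease during the trial".

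The primary endpoint (2.7.1) is built from disease complications: a second decompensating event, rebleeding, recurrent ascites or encephalopathy, spontaneous bacterial peritonitis, hepatorenal syndrome and jaundice.

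On adherence, section 2.11 states: "Adherence will be calculated as (actual dose taken/prescribed dose) × 100% over the 48-week treatment period". Good adherence runs from 80% to 100%, and "Participants with adherence <80% will be classified as having poor adherence". Intake above 100% is a protocol deviation, and "these participants will not be classified as good adherence and will be excluded from the per-protocol population". The share with good adherence is compared between arms by chi-square test.

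**The concern.** A PP set is meant to show the treatment effect in patients who followed the protocol. Here, entry requires reaching the end of treatment, which a patient may fail to do because of the outcome under study. Death before week 48 always excludes. A non-fatal endpoint event excludes whenever treatment stops, and section 2.9 gives grounds for that in many endpoint patients. The arm with more events then loses more patients, and those it loses are the ones with events. The PP result becomes a comparison of patients selected after randomization, which weakens it as a check on ITT.

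The adherence score may carry the same dependence. If the denominator is the full 48-week dose, early stopping lowers the score however well the patient took the tablets until then, so the between-arm adherence test partly reflects event rates. Separately, the exclusion above 100% has no margin for counting error.

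**Working it through.** **Inputs.** From section 2.10: 48-week event rates of 53.7% (Fuzheng Huayu) and 67.5% (control), 194 per arm before dropout, 10% dropout, 216 per arm. From section 2.6: 4 tablets three times a day for 48 weeks.

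**The plan's own figure.** The printed formula gives (1.96 + 0.842)² × (0.537 × 0.463 + 0.675 × 0.325) / 0.138² = 192.9, so 193 per arm; the pooled-variance version gives 196. The stated 194 lies between them, and 194 / 0.9 = 215.6, so 216. The sample size is not in question.

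**PP set.** Planned events are 216 × 0.537 = 116 and 216 × 0.675 = 145.8, about 146. Let f be the share of endpoint patients who stop treatment before week 48. The documents do not give f, so it is an assumption, taken as equal in both arms. With event rate p, PP size is 216 × (1 − f × p), PP events are 216 × p × (1 − f), and the excluded share is f × p. Other reasons for exclusion are ignored.

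| f | Excluded | PP patients | PP events | PP event rate | Difference (points) |
|---|---|---|---|---|---|
| 0% | 0% vs 0% | 216 vs 216 | 116 vs 146 | 53.7% vs 67.5% | 13.8 |
| 25% | 13.4% vs 16.9% | 187 vs 180 | 87 vs 109 | 46.5% vs 60.9% | 14.4 |
| 50% | 26.9% vs 33.8% | 158 vs 143 | 58 vs 73 | 36.7% vs 50.9% | 14.2 |
| 75% | 40.3% vs 50.6% | 129 vs 107 | 29 vs 36 | 22.5% vs 34.2% | 11.7 |
| 100% | 53.7% vs 67.5% | 100 vs 70 | 0 vs 0 | none | none |

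The primary model is a Cox model, so the hazard-ratio scale matters too. Taking the ratio of ln(1 − event rate) in the two arms under proportional hazards, the implied hazard ratio is 0.685 at f = 0%, then 0.666, 0.642 and 0.609 at 25%, 50% and 75%. The difference in rates stays near 14 points up to f = 50%, while the hazard ratio moves away from 1 through selection alone.

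**Adherence, on the full-period reading.** The full prescription is 12 × 7 × 48 = 4,032 tablets, and 80% of 48 weeks is 38.4 weeks. A patient who takes every tablet but stops before week 38.4 scores below 80%; stopping at week 24 gives 24 / 48 = 50%. With a constant event hazard over the 48 weeks (assumption), the share scored as poor adherers purely through stopping at the event is f × [1 − (1 − p)^0.8]:

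- f = 100%: 46.0% vs 59.3%. A two-sided 5% test with 216 per arm would flag this with about 79% probability.
- f = 50%: 23.0% vs 29.7%, flagged with about 35% probability.
- f = 25%: 11.5% vs 14.8%, flagged with about 17% probability.

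**Upper limit.** 4,033 / 4,032 = 100.02%, which is above 100% and excludes the patient from PP.

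**The case against.** The PP rule turns on completing treatment, not on staying event-free, and no passage stops treatment at a primary event. A reader might infer that every endpoint patient leaves PP, so that its event rate is near zero by construction and it can tell us nothing about ITT. The documents do not support that. Section 2.9 does not name every endpoint component: a bilirubin rise that counts as jaundice, for example, need not lead to withdrawal. A patient who stays on treatment to week 48 remains in PP. The 100 vs 70 row is the extreme of a range, and at 25% to 50% stopping the difference in event rates is largely kept. This part of the objection stands.

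On adherence, the prescribed dose may mean the dose prescribed while the patient was still on treatment, with the 48 weeks only marking the observation window. On that reading the fully compliant patient who stops at week 24 scores 100%. The full-period reading is the likelier one, but it is not the only one.

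A reader might also infer that very low intake is allowed in PP because only intake above 100% is expressly excluded. That does not follow. PP also requires no major protocol violation, the article does not list those violations, and the full protocol or SAP may include low adherence.

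Finally, ITT includes all randomized patients, and the article gives PP no stated decision role. That limits the consequence but does not make the PP definition sound.

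**Conclusion.** The point holds in limited form. As written, PP membership depends on the outcome: always for deaths before week 48, and for non-fatal endpoint patients whenever they stop treatment. With the planned event rates and equal stopping shares in both arms, exclusion differs by arm, from 13.4% vs 16.9% at 25% stopping to 53.7% vs 67.5% at 100%. The true stopping share is unknown. How far the adherence comparison is affected depends on the denominator reading and on event timing. The missing tolerance above 100% is plain from the text. ITT is unaffected by these definitions. Severity is minor, with high confidence on the PP set and moderate confidence on adherence.

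**What to change.** - Define PP as randomized participants with no major protocol violation up to the first of primary event, death or week 48.
- Compute adherence as doses taken divided by doses prescribed up to that same date, or to permanent discontinuation if earlier.
- Put a stated tablet-count tolerance on the exclusion for intake above 100%.
- Reconcile the PP definition with the withdrawal criteria in section 2.9, including how a patient withdrawn for a serious adverse event that is not an endpoint is classed. No change to any clinical rule is proposed here.

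The cost is a few sentences. The tablet counts are already implied by the planned adherence analysis, and the sample size stays at 432. A fully compliant patient would then score 100% whenever the event occurs, and the planned 116 and 146 events would not be lost from PP through early stopping.

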#### Primary endpoint

2.7.1

The cumulative incidence of further decompensation events is defined as any of the following in cirrhotic patients 48 weeks after the first decompensation: (1) Development of a second portal hypertension - driven decompensating event (ascites, variceal bleeding, or hepatic encephalopathy) and/or jaundice; (2) Recurrent variceal bleeding, recurrent ascites (≥3 large-volume paracenteses within 1 year), recurrent encephalopathy, spontaneous bacterial peritonitis (SBP) and/or hepatorenal syndrome - acute kidney injury (HRS-AKI); (3) In patients with bleeding alone, development of ascites, encephalopathy, or jaundice after recovery from bleeding (not during the bleeding episode); (4) After the first decompensation, the new increase of total bilirubin >51.3 μmol/L (3 mg/dL) was judged as jaundice (de Franchis et al., 2022).

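### LOCF is stated for all missing ITT efficacy data without exempting the primary endpoint; this does not fit the Cox time-to-event analysis and, taken literally, biases it when dropout differs between arms

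*Protocol article*

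**What the plan says.** Section 2.11 (Data analysis plan) puts everyone who was randomized into the ITT analysis, "analyzed according to their original randomized assignment regardless of whether they received the assigned treatment or completed the study". It then gives the article's only rule for missing data: "if the data related to the efficacy are missing, the method of last observation carried forward (LOCF) will be used to fill in". The rule covers efficacy data in general and names no exception.

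The effectiveness paragraph of the same section treats the primary endpoint as a time to event: "For the primary time-to-event efficacy endpoint, a Cox proportional hazards model will be used to estimate the treatment effect". It adds that "The Kaplan-Meier method and log-rank test will be used for descriptive and unadjusted comparisons", and the section opens by mentioning competing-risk analysis. For other outcomes, "For binary efficacy outcomes, logistic regression adjusted for study center and relevant baseline covariates will be used", and changes from baseline are compared by t-tests or rank-sum tests.

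Section 2.7.1 defines the primary event as "any of the following in cirrhotic patients 48 weeks after the first decompensation". Section 2.10 reaches 216 per group after "Accounting for a 10% dropout rate". Section 2.9 lists serious adverse events and severe disease changes or complications among the grounds for withdrawal. Nothing says how the LOCF rule and the time-to-event methods are to be combined.

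**The concern.** The two rules build different data for the same patient. Someone lost at week 20 with no event contributes 20 weeks at risk under the Cox model and is then censored. If LOCF is applied to event status, the same patient is carried to week 48 as event-free, which adds 28 weeks of risk time that nobody observed.

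Two things are at stake. The week-48 incidence is understated in both arms. And if one arm loses more patients before an event, that arm looks better for a reason unrelated to treatment, so the type I error of the primary comparison is no longer 5%.

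The withdrawal grounds make this more than a formality: disease complications lie close to the primary event itself, so a patient may leave while deteriorating and be carried forward as well. The rule also reaches the binary and change-from-baseline outcomes, where no censoring replaces it.

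**Working it through.** **Inputs from section 2.10.** Event rates at 48 weeks of 53.7% (combination) and 67.5% (antiviral alone); a "two-sided Z-test for two independent proportions with α = 0.05 and power = 80" per cent; 10% dropout; 216 per group. Dropout by arm is not given, so arm-specific rates below are assumptions.

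**The plan's own figure.** (1.96 + 0.842)² × (0.537 × 0.463 + 0.675 × 0.325) / 0.138² = 7.851 × 0.4680 / 0.01904 = 192.9, so 193; the pooled-variance version gives 196. The stated 194 is consistent with these, and 194 / 0.9 = 215.6, so 216 per group and 432 in all. The sample size does not depend on the LOCF rule.

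**Model for the literal reading.** Constant hazard h = −ln(1 − p) over 48 weeks from randomization. A fraction D of patients has a dropout time uniform over the 48 weeks and independent of outcome. The probability of an event before that dropout time is q = 1 − (1 − e^(−h))/h.

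- p = 0.675: h = 1.124, q = 1 − 0.675/1.124 = 0.399.
- p = 0.537: h = 0.770, q = 1 − 0.537/0.770 = 0.303.

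Events recorded before dropout are kept, so the apparent incidence under LOCF is (1 − D)p + Dq.

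**Share affected at D = 10%.** 0.10 × (1 − 0.399) = 6.0% of the control arm and 0.10 × (1 − 0.303) = 7.0% of the treated arm.

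**Equal 10% dropout at the planning rates.** Control: 0.9 × 67.5 + 0.1 × 39.9 = 64.7%. Treated: 0.9 × 53.7 + 0.1 × 30.3 = 51.4%. The difference is 13.4 points, against 13.8 planned. With no true effect the two arms shift equally and the error stays at 5.0%.

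**No true effect (67.5% in both arms), dropout 5% versus 15%.**

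- 5% arm: 0.95 × 67.5 + 0.05 × 39.9 = 66.1%.
- 15% arm: 0.85 × 67.5 + 0.15 × 39.9 = 63.4%.
- False difference: 0.10 × (67.5 − 39.9) = 2.8 points.
- Two-proportion test at 216 per arm: the standard error is about 4.6 points and the critical difference about 9.0 points. The probability of rejecting in favour of the arm with more dropout is 1 − Φ((9.0 − 2.8)/4.6), about 8.7%. In the other direction it is about 0.5%. The total is 9.2%.

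**Check with another dropout model and the log-rank test.** With exponential dropout at 15% versus 5% and no true effect, the false difference is 2.9 points and the error 9.6% as proportions. In 4,000 simulated trials the log-rank error was 8.8% with LOCF to week 48 (hazard ratio about 0.94) and 4.6% with censoring at dropout (hazard ratio about 1.00). As an upper bound, if all dropouts left at baseline, the false difference would be 0.10 × 67.5 = 6.8 points and the error about 30%.

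**Direction under the planning rates (exponential dropout, LOCF, two-proportion test).**

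| Dropout, FZHY / placebo | Apparent difference | Power |
|---|---|---|
| none | 13.8 points | 84% |
| 10% / 10% | 13.4 points | 81% |
| 15% / 5% | 16.0 points | 92% |
| 5% / 15% | 10.7 points | 62% |

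With censoring, the log-rank hazard ratio stays near 0.68 in all three dropout scenarios.

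**The case against.** The strongest reply is that the Cox, Kaplan-Meier and log-rank methods already settle the matter. A censored time is not a missing value, LOCF sits more naturally with the visit-based change-from-baseline tests, and a condensed article may leave censoring details to the full protocol. It stands in part: extending event-free time to week 48 is the literal reading, not the only one. But the LOCF sentence is a stated rule, not an omission, and as written it includes the primary endpoint.

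The scale also depends on chosen scenarios. The only documented dropout rate is 10% overall, and at equal dropout, independent of outcome, LOCF does little harm. That stands.

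Several stronger readings are tempting and not supported:

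- A reader might infer that every dropout is recorded as event-free. LOCF would carry forward an event already recorded, and in the model above about 40% (control) and 30% (treated) of dropouts had one.
- A reader might expect more dropout on FZHY from the tablet burden. Section 2.6 gives the placebo arm the same number of tablets, so burden alone gives no reason for a difference.
- A reader might infer a bias towards FZHY. If the drug works, withdrawals for complications could be more frequent on placebo, and LOCF would then work against it.
- A reader might infer that LOCF freezes continuous outcomes at a better value. Both arms receive antivirals and improvement is among the outcomes, so the frozen value could equally be worse.
- A more extreme split, 5% versus 25%, gives 5.5 points and about 22% error, but it averages 15%, above the planned rate.

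**Conclusion.** The concern holds in this form: an LOCF rule without exemption is not reconciled with the time-to-event analysis of the primary endpoint and gives a wrong result if followed literally. The size ranges from almost nothing (equal 10% dropout) to roughly a doubling of the type I error (about 9% at an assumed 5% versus 15%).

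These figures assume constant hazard and dropout independent of outcome, and the arm-specific dropout rates are not in the document. Independence is doubtful given section 2.9. If dropout is informative to a different degree in the two arms, equal dropout rates would not rule out bias, and censoring alone would not remove it. The documents do not allow the direction to be predicted.

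**What to change.** In section 2.11:

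1. Exempt time-to-event endpoints from LOCF, and state that patients without an event are censored at their last documented outcome assessment.
2. Take week-48 proportions from the cumulative incidence estimator, in line with the competing-risk analysis already mentioned.
3. Replace LOCF for continuous and binary efficacy outcomes with a method valid under missing at random, such as a mixed model for repeated measures or multiple imputation.
4. Add one sensitivity analysis for informative dropout on the primary endpoint (tipping-point or delta-adjusted), because censoring assumes non-informative dropout.

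The cost is analysis wording and modest programming. The change should be made before unblinding.

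### The primary Cox model is stated with treatment and centre only, and continuous outcomes are tested on raw change, so efficiency available from baseline data is forgone

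*Protocol article*

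**What the plan says.** All of this is in section 2.11 of the protocol article.

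- **Primary endpoint.** A Cox proportional hazards model is planned "with treatment group as the main factor and study center included as a stratification factor or covariate". Kaplan-Meier curves and the log-rank test are kept for description and unadjusted comparison.
- **Binary efficacy outcomes.** In the next part of the same paragraph, "logistic regression adjusted for study center and relevant baseline covariates will be used". The covariates are not named.
- **Continuous outcomes.** "Between-group comparisons of changes from baseline will be performed using independent-sample t-tests or Wilcoxon rank-sum tests". Neither the baseline value nor centre enters the comparison.
- **Categorical changes.** "Changes in the two groups before and after treatment were analyzed using the chi-square test".

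Elsewhere, section 2.5 stratifies randomisation by centre alone. Table 2 marks liver function, coagulation and renal function as required at V1. Section 2.4 admits patients whose first event may be ascites, variceal bleeding, hepatic encephalopathy or hepatorenal syndrome.

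**The concern.** The primary analysis uses less baseline information than the analysis of binary outcomes, and no reason is given.

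The protocol itself suggests that baseline status bears on the endpoint (section 2.7.1). Recurrent variceal bleeding presupposes an earlier bleed. Clause 3 applies only to patients whose first event was bleeding alone. Clause 4 turns on total bilirubin rising above 51.3 μmol/L, so the starting bilirubin matters. Because only centre is stratified, the design does not balance the type of first event or liver severity. Section 2.11 plans tests of baseline balance but attaches no consequence to them, so any adjustment made after seeing an imbalance would be open to the charge of being post hoc.

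If baseline values predict the outcome, a Cox model that omits them gives a hazard ratio nearer to 1 and less power. For continuous outcomes, a change-score comparison is less precise than ANCOVA unless baseline and follow-up are almost perfectly correlated. The planned effect comes from retrospective data that pool three herbal products, so some reserve of power would be welcome.

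**Working it through.** **Inputs from section 2.10.** A "two-sided Z-test for two independent proportions with α = 0.05 and power = 80% (β = 0.20"). The treated rate: "the 48-week cumulative incidence of further decompensation was 53.7% in patients who received commercial Chinese polyherbal preparation (CCPP") plus antiviral therapy. The control rate: "67.5% in patients who received antiviral therapy alone". Then, "with a 1:1 allocation ratio, the required sample size per group was calculated as 194 using the formula".

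**Step 1: reproduce the planned size.** With the article's formula:

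n = (1.96 + 0.842)² × (0.537 × 0.463 + 0.675 × 0.325) / (0.675 − 0.537)² = 7.851 × 0.4680 / 0.01904 = 192.9, so 193 per group.

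The pooled-variance version gives 196. The stated 194 lies between them and is accepted. 194 / 0.9 = 215.6, so 216 per group and 432 in total, as stated.

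**Step 2: power of the planned Cox model.** Under proportional hazards the two rates imply HR = ln(1 − 0.537) / ln(1 − 0.675) = 0.685. Expected events at 194 per group are 194 × (0.537 + 0.675) = 235. Schoenfeld's formula needs 4 × 7.851 / (ln 0.685)² = 220 events for 80% power, and 235 events give 82.6%. The planned model therefore meets its target on the protocol's own inputs.

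**Step 3: add one baseline score.** The simulation used 194 per group, exponential event times, censoring at 48 weeks, and marginal event rates held at 53.7% and 67.5%. There was one standard normal baseline score, with 3000 trials per setting. The documents do not give the score's strength, so it is assumed over a range.

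| Assumed HR per SD of score | True conditional treatment HR | Power, score omitted | Power, score included |
|---|---|---|---|
| 1.0 (uninformative) | 0.685 | 84% | 84% |
| 1.25 | 0.679 | 83% | 84% |
| 1.5 | 0.666 | 82% | 87% |
| 2.0 | 0.632 | 84% | 94% |
| 2.5 | 0.599 | 85% | 97% |

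Simulation error is about 1.4 points on each power. The gain is about 1, 5, 10 and 12 points in the last four rows. It comes through a conditional hazard ratio further from 1 (at 2.0 per SD, an average estimate of 0.63 adjusted against 0.68 unadjusted), not through a smaller standard error.

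**Step 4: continuous outcomes.** Take equal variance σ² at baseline and follow-up, and correlation r. The per-patient variance is 2σ²(1 − r) for the change score and σ²(1 − r²) for ANCOVA. The ratio of ANCOVA to change score is (1 + r)/2. The extra patients a change-score test needs for equal precision are 2/(1 + r) − 1.

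| Assumed r | Variance ratio | Extra patients for change score |
|---|---|---|
| 0.3 | 0.65 | 54% |
| 0.5 | 0.75 | 33% |
| 0.7 | 0.85 | 18% |
| 0.8 | 0.90 | 11% |

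**Step 5: the chi-square sentence.** It has two readings. If before and after proportions are compared within a group, the same patients are counted twice and the ordinary chi-square test wrongly assumes independence. If categories of change are compared between arms, the samples are independent and the test is valid. The wording does not settle which is meant.

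**The case against.** The strongest reply is that nothing here is an error. A Cox model with treatment and the randomisation factor is a conventional, valid primary analysis, and Step 2 shows that it reaches the stated power. Change-score tests are also valid under randomisation, and the continuous outcomes are secondary. This stands: a reader might infer bias or an underpowered trial, and the documents support neither.

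Second, the covariates' strength is assumed. The protocol gives no association between any baseline value and further decompensation, so it cannot be said that strongly prognostic information is being thrown away. At a hazard ratio of 1.25 per SD the gain is about one point. This also stands, and is why the result is given as a range.

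Third, the article condenses a fuller plan, which might add covariates. It is true that the text does not bar others. But the Cox model and the change-score tests are stated methods, and the contrast with the binary outcomes is on the page. The point concerns what is written, not what is left out.

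Fourth, a reader might take the chi-square sentence as an unpaired test of paired data. The same paragraph uses paired t-tests and signed-rank tests for within-group change, so the authors do distinguish pairing, and the between-arm reading is open. Only a request to clarify is justified.

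Fifth, Table 2 lists test panels. It does not name albumin, INR or the type of first event as items. Their collection is likely, since the first event is an eligibility criterion and medical history is taken at V1, but it should be confirmed.

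**Conclusion.** The point holds as one of efficiency, and the change is worth making. The planned between-arm comparisons are valid and the sample size reproduces. Adjusting the primary model for baseline severity would add between about 1 and 12 points of power at 194 per arm, for assumed score hazard ratios of 1.25 to 2.5 per SD, and costs nothing if the score proves uninformative. ANCOVA would cut the variance for continuous outcomes by 10% to 35%, for assumed correlations of 0.8 down to 0.3 and equal variances at the two times. The power figures rest on proportional hazards, the retrospective event rates of section 2.10 and complete follow-up of 194 per arm. The adjusted hazard ratio is a different, conditional quantity and must be labelled so. The chi-square sentence is unclear, not demonstrably wrong.

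**What to change.** - **Primary Cox model.** Besides centre, name in advance a short list of baseline covariates: type of first decompensation, and one liver-severity score or its components. State that the hazard ratio is conditional on them. Report the unadjusted hazard ratio beside it, with the log-rank test already planned.
- **Continuous outcomes.** Replace the tests on change by ANCOVA of the follow-up value on treatment, baseline value and centre. Use a transformed or rank-based version for skewed laboratory markers.
- **Chi-square sentence.** Say which comparison is meant. For a within-group before-after proportion, use a paired test such as McNemar. For a comparison between arms, use the logistic model already planned, with baseline status included.

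The cost is analysis wording, fixed before unblinding, and a check that the case report form holds the chosen covariates. No extra patients or visits are needed.
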